#### Sham blinding

2.4.5

The Magstim Double 70 mm Air Film sham coil has a figure-of-eight winding with components that largely cancel the field produced under the center of the coil. The sham coil is designed to simulate the sounds and vibrations of the active coil while inducing superficial currents using a brief pulse of electromagnetic energy that is not sufficient to stimulate the cortex. The Magstim Double 70 mm Air Film sham coil additionally mimics the cutaneous sensations (e.g., tingling, muscle twitching) that are produced by the active version of the coil. Previous validation testing on earlier models of the Magstim sham coils using TMS-naïve volunteers indicate validity with 12 of 15 participants in the sham group and 11 of 13 participants in the active group believing they received active stimulation (50). We therefore believe that this coil has equal or better blinding than previous models. Nonetheless, we plan to enroll only TMS-naïve participants to preserve blinding since participants who have experienced active TMS may be able to distinguish active from sham TMS more easily.

To further protect the blind, the study team has a strict data collection and management plan. Site staff only have access to data and collection forms that are required for their role. We collect information about the validity of the blind from both the participant and TMS operator, after the first TMS session and at completion of the final TMS session, in two separate self-report measures. The self-report blinding assessments are inaccessible to blinded staff so as not to bias their outcome scoring. Role permissions and randomization in the electronic data capture system are handled and maintained separately by an unblinded data management team.

#### Resting motor threshold

2.4.6

Prior to the first rTMS session, resting motor thresholds are assessed by a privileged provider at each site by administering several single pulses of TMS over the left (dominant) motor cortex. The locations of the appropriate part of the motor cortex are initially estimated as approximately 5 cm lateral to the vertex of the head, and the location/intensity of stimulation is titrated using a parameter estimation by sequential testing (PEST) algorithm (51) until a contraction is visually observed in the contralateral abductor pollicis brevis or the first digital interosseous muscle 50% of the time.

#### Intervention: aiTBS sessions

2.4.7

Figure 3 illustrates the intervention phase of the study, which consists of 40 iTBS sessions provided over a 1-week (five business days) period (eight sessions/day Monday–Friday). Eight sessions/day are used instead of the 10 sessions/day used in the SNT protocol because of logistical and staffing constraints at the research sites. Each iTBS session consists of 60, 2-s, trains of 10 bursts. Bursts are applied every 200 ms (5 Hz). Each burst consists of three pulses of rTMS at 50 Hz. There is an 8-s intertrain interval such that each session takes approximately 9 min and 30 s in total. Stimulation sessions are delivered every 60 min (50-min break from the end of one session to the beginning of another). Stimulation is delivered at 90% of resting motor threshold at the cortical target and corrected for scalp-to-target distance (48). If the participant cannot tolerate 90% of resting motor threshold at the first session, a titration schedule is followed such that they are allowed to receive as low as 70% of resting motor threshold on the first and second sessions, and 80% on the third session. All participants must receive iTBS at 90% of resting motor threshold by the fourth session and remain at this intensity for the rest of the treatment protocol.

**Figure 3 fig3:**
[figure not shown]
Accelerated intermittent theta burst stimulation. **(A)** iTBS sessions consist of 60, 2-s, trains of 10 bursts. Bursts consist of three rTMS pulses at 50 Hz applied every 200 ms (5 Hz). An 8-s interval separates each train; the total time it takes to complete 60 trains in a session is approximately 9 min and 30 s. **(B)** The intervention phase consists of 40 iTBS sessions provided over a consecutive 5 business day period with 8 sessions provided per day. The 5-day period may take place over a 7 calendar-day week.

Primary analyses will be conducted with an intention to treat manner with all participants who receive at least one session of aiTBS. A secondary analysis will be done per protocol including participants who complete at least 32 of the 40 sessions (80%).

#### Baseline, post aiTBS, and follow-up behavioral evaluations

2.4.8

Participants complete several self-report questionnaires, structured interviews, and MRI scans both for determination of eligibility as well as baseline symptom characterization, aiTBS targeting, and functional network mapping. The Post-aiTBS and follow-up evaluations consist of repeating assessments and MRI scans that were conducted at the Baseline Evaluation (see Supplementary Table S3 for a list of measures that are administered over the course of the study). The Post-aiTBS Evaluation is conducted within 10 working days of the participants’ final rTMS session. Participants then complete regular follow-up evaluations for up to a total of six-monthly sessions.

Participants are afforded the opportunity to opt in or out of individual follow-up evaluations. The research team make up to four attempts to contact the participant via phone/email. If the participant fails to respond to the study team’s attempts at contact, it is considered an unwillingness to participate during the specified month. Contact with the participant is reinitiated for the subsequent follow-up evaluations. If they choose not to participate in follow-up evaluations, their data may not be included in secondary outcome analyses related to follow-up time points. During the Follow-up phase of this study, participants are allowed to change their treatment regimen including the addition of new or modified interventions (psychopharmacological, behavioral, or device-based treatments). The study team monitor these changes and they are also integrated into the statistical model as co-variates for the secondary outcome analyses related to follow-up time points.

To ensure robust administration and scoring of the study’s primary outcome measure, the study team has developed a comprehensive training plan to standardize MADRS administration across performance sites. The MADRS administration training plan utilizes a 4-phase format that required (1) didactic reading, (2) observations, (3) practice sessions, and (4) certification by a trained investigator. Trainers utilize a Rater Applied Performance Scale (RAPS) (52), which has been applied to neuropsychological assessment training, to objectively rate the administrator’s performance; a score of 3 or higher on a 4-point Likert scale indicates a “good” performance and subsequent certification. In general, most MADRS administrations for each individual participant are performed by the same team member.

#### Optional maintenance aiTBS sessions

2.4.9

Participants who complete at least 32 randomized aiTBS sessions, achieve treatment response (≥50% improvement in MADRS), and experience a remission of symptoms (MADRS ≤ 10) at the Post-aiTBS evaluation, followed by a relapse of depressive symptoms (defined as MADRS ≥ 15) during the course of the six-month Follow-up period will be offered optional Maintenance aiTBS sessions. Regardless of randomized group assignment (i.e., active arms vs. sham arm), optional Maintenance aiTBS sessions will be offered to all participants who meet the specified criteria. Participants will be able to take part in Maintenance sessions regardless of original group assignment (i.e., the study will remain double-blinded). If the participant meets the above criteria and expresses interest in receiving the optional Maintenance aiTBS sessions, the research team will perform an additional screening process to confirm continued eligibility including completion of a screening form as well as conducting a review of relevant medical records inclusive of records that have been entered into the EMR system since the initial baseline review.

The Maintenance course of aiTBS will be identical to the initial randomized phase of the study where the participant will receive up to 40 sessions of aiTBS across 5 business days (Monday–Friday). Resting motor threshold will be re-assessed since it may change over a several month period. Participants will receive the same protocol they received during the Randomization phase during this optional Maintenance phase and will remain blinded. Participants who decline or do not complete the Maintenance sessions may continue to take part in the Follow-up Phase of the study. Participants will only be able to partake in a single Maintenance course during the six-month follow-up period and will not be able to partake in any additional Maintenance courses of aiTBS as part of the research study. Maintenance treatments or other major changes to their clinical regimen will be considered as co-variates in secondary analyses of outcomes obtained during the Follow-up Phase of the study.

### Data analysis

2.5

#### Primary analysis of primary efficacy outcome

2.5.1

We propose a Bayesian adaptive trial with interim analyses allowing for dropping of inferior active arms as well as futility and success stopping. The trial will begin by enrolling all three arms (sham and 2 active arms) in a 1:1:1 allocation with non-informative prior probabilities that any arm is superior to any other arm. Interim analyses will be conducted when *N* = 90 and *N* = 135 have been enrolled. At each interim analysis the following adaptations may be made

Arm dropping – If either active arm has a 60% or greater Bayesian posterior probability of being superior to the other active arm, the inferior active arm will be dropped from the study, with the remaining trial maintaining the 2:1 active:sham randomization, but with only one active arm.Futility stopping – If neither active arm has greater than a 60% Bayesian posterior probability of being superior to sham (this will occur only if both arms are performing only slightly better than sham or worse), then the entire trial will stop for futility. This will provide proper stewardship of resources by not continuing a trial that is unlikely to yield a successful conclusion.Success stopping – If either active arm obtains a 99.75% posterior probability of being superior to sham, the trial will stop for success. If this high bar is met early, the trial will allow early dissemination of this successful result. Reaching this high bar will require very convincing data at an interim analysis.

If the trial continues to the maximal sample size, then the trial will be deemed successful if either active arm achieves a 99% posterior probability of superiority to sham. The 99% threshold was determined through simulation (see FDA guidance on adaptive trials). When combined with the early stopping rules, the full trial will maintain 2.5% type 1 error accounting for both the multiplicity of 2 arms and the 2 interim analyses, based on 100,000 simulations.

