**Figure 1 fig1:**
[figure not shown]
Bayesian adaptive trial schema. The Bayesian adaptive trial for accelerated intermittent theta burst stimulation (aiTBS) with interim analyses at *N* = 90 and *N* = 135. Participants (*N* = 198) are randomized 1:1:1 to (1) active rsfMRI-based targeted aiTBS, (2) active scalp-based (Beam F3) targeted aiTBS, or (3) sham aiTBS. Adaptations include dropping inferior arms (if either active arm has a 60% or greater Bayesian posterior probability of being superior to the other active arm), stopping for futility (if neither active arm has greater than a 60% Bayesian posterior probability of being superior to sham), or stopping for success (if either active arm obtains a 99.75% posterior probability of being superior to sham) if predefined Bayesian probabilities are met. This design ensures efficiency, ethical resource use, and improved participant outcomes while maintaining statistical rigor.

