### Participants

2.2

The study sample includes up to 198 male and female current or former SMs, eligible for care at Department of Defense (DoD) or Veterans Administration (VA) facilities, between the ages of 18 and 55, with a history of concussion and the presence of depressive symptoms. Depending on the results of the interim analyses, the actual sample size may differ and is flexible between 99 and 198 participants. We also anticipate 10% attrition between consent and first treatment thus accounting for 90–180 participants with primary outcome measures for analysis.

The study is being conducted at two military treatment facilities (MTF) [William Beaumont Army Medical Center (WBAMC) and Alexander *T. Augusta* Military Medical Center (ATAMMC) and one VA Medical Center (VAMC) (VA Palo Alto)]. Interested participants are initially provided information about the study and prescreened for eligibility based on inclusion and exclusion criteria. This includes age, history of a mTBI/concussion (excluding moderate, severe, or penetrating TBI), presence of depressive symptoms, and absence of metal, brain lesion, implanted devices, or other exclusionary conditions (see Supplementary Table S1 for more detailed inclusion/exclusion criteria).

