### Power analysis for primary efficacy outcome

2.3

During the initial design phases, the trial was simulated under a variety of alternative scenarios to assess power. For example, if one of the arms had a 4-point improvement over sham, the power was 81–82% with an expected sample size of 150 patients. Alternatively, 95% power and an expected sample size of 137 patients was obtained if one of the arms had a 5-point improvement over sham. If both arms were equal to sham (e.g., the null hypothesis), then the expected trial sample size was 147 patients. This expected sample size is an average of the three possible trial sizes averaged over the probability each sample size occurs [i.e., 99 (if the trial stops after the first interim analysis), 148 (if the trial stops after the second interim analysis), or 198 (if the trial continues to enroll until the maximum number of participants have completed the study)], assuming 10% dropout rate.

The interim analyses allow for efficient stewardship of resources. While there is no guarantee the trial will stop before the maximal sample size, there is substantial probability of meaningful sample size savings based on the outcomes of these scenarios. We also utilize a gatekeeping approach by making the testing of secondary outcomes dependent on the success of the primary analysis.

The Bayesian adaptive approach allows for simultaneous examination of the two arms compared to sham, thus resulting in a more efficient trial. Accumulation of data over the course of the trial is utilized to focus enrollment on the treatment arm that demonstrates superior efficacy. By focusing resources on the better performing arm, we obtain equivalent power as a nonadaptive trial with a high probability of sample size savings, as well as treating participants within the trial better than using equal randomization among all three arms (42).

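### The interim looks are triggered at 90 and 135 enrolled, but the design is sized with 90 and 135 as participants who have the primary outcome

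*Protocol article*

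**What the plan says.** Four places in the protocol article bear on when the looks fall.

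- Section 2.5.1 (primary analysis): "Interim analyses will be conducted when *N* = 90 and *N* = 135 have been enrolled".
- Figure 1 caption: "with interim analyses at *N* = 90 and *N* = 135. Participants (*N* = 198) are randomized 1:1:1". It does not say whether 90 and 135 are counted on the same basis as the 198.
- Section 2.3 (power): the possible trial sizes are "99 (if the trial stops after the first interim analysis), 148 (if the trial stops after the second interim analysis", or 198 at the maximum, "assuming 10% dropout rate".
- Section 2.2 (participants): "the actual sample size may differ and is flexible between 99 and 198 participants", and "We also anticipate 10% attrition between consent and first treatment thus accounting for 90–180 participants with primary outcome measures for analysis".

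Section 2.3 also gives expected sample sizes: 147 under the null, 137 at 5 points with 95% power, and at 4 points "the power was 81–82% with an expected sample size of 150 patients".

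**The concern.** The number 90 is an enrolled count in the rule that starts the interim and an analysable count in the sections that size the trial. The two differ by the 10% attrition. Arm dropping, futility and early success all act at these looks, so the trigger decides how much information each adaptation uses. If the looks run as written, each is taken with about 10% fewer outcomes than the sizing assumes, and fewer still if some enrolled participants await the Post-aiTBS evaluation, which section 2.4.8 allows up to 10 working days after the last session.

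Two smaller figures belong to the same set: the conversion between enrolled and analysable numbers, and the expected sample size at 4 points.

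**Working it through.** **1. Which count is 90?**

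Inputs: 90 and 180 with the primary outcome (2.2); 99, 148 and 198 enrolled (2.2, 2.3); looks at 90 and 135 (2.5.1).

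- 90 × 1.1 = 99
- 135 × 1.1 = 148.5 (stated as 148)
- 180 × 1.1 = 198

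So in the sizing, 90, 135 and 180 are analysable participants and 99, 148 and 198 are the enrolled totals.

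**2. Reproducing the stated null figure**

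The rules of section 2.5.1 were simulated with a normal outcome, a flat prior, equal allocation and then 2:1 active to sham after an arm is dropped. Thresholds were 60% (arm dropping and futility), 99.75% (interim success) and 99% (final success).

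| Reading | Analysable at looks | Trial size at stop | Null expected N |
|---|---|---|---|
| As sized in 2.2 and 2.3 | 90 / 135 / 180 | 99 / 148 / 198 | about 147 (stated: 147) |
| As worded in 2.5.1 | 81 / 121.5 / 178.2 | 90 / 135 / 198 | about 141 |

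Under the null with a flat prior the result does not depend on the SD, so this comparison needs no assumed SD. Nearly all of the 6-participant gap comes from counting a stop as 90 or 135 instead of 99 or 148. It identifies which design was simulated; it does not measure harm.

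**3. Effect on the first look if the trigger is read literally**

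90 × 0.9 = 81 analysable, or 27 per arm instead of 30. Assume SD 7.35, a 4-point effect in one arm and none in the other. (7.35 returns the stated power; the article gives no SD.) Success needs z of at least 2.807, the 99.75% normal quantile.

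- 30 per arm: SE = 7.35 × √(2/30) = 1.898; 4/1.898 = 2.108; P(Z > 2.807 − 2.108) = P(Z > 0.699) = 24.2%
- 27 per arm: SE = 7.35 × √(2/27) = 2.000; 4/2.000 = 2.000; P(Z > 0.807) = 21.0%

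The full simulation, which also allows the null arm to succeed by chance, gives about 24% and 21%. Overall power goes from 81.7% to 81.2%. Simulated type I error is about 1.9% either way.

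**4. Attrition arithmetic**

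Losing 10% means multiplying enrolment by 0.9:

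- 99 × 0.9 = 89.1; 148 × 0.9 = 133.2; 198 × 0.9 = 178.2
- conversely, 90/0.9 = 100; 135/0.9 = 150; 180/0.9 = 200

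The stated totals multiplied by 1.1 instead of dividing by 0.9. The gaps are 1, 2 and 2 participants.

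**5. Expected sample size at 4 points**

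The SD and the other arm's effect are not stated. The SD was solved so that power at 4 points is 81–82%, separately for each assumed effect in the other arm.

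| Other arm's effect, as a share of 4 points | Solved SD | Power | Expected N |
|---|---|---|---|
| −25% | 7.45 | 81.2% | 158.5 |
| 0 | 7.40 | 81.2% | 158.2 |
| 50% | 7.19 | 81.4% | 156.7 |
| 100% | 8.17 | 81.2% | 156.9 |

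Across further variants that keep the stated thresholds, the range is about 155 to 160, against the stated 150. At 5 points, the same SDs give 94.9–95.4% power and an expected N of 136 to 139, which agrees with the stated 95% and 137.

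**The case against.** The intent can be recovered from sections 2.2 and 2.3, so this may be no more than loose wording. Section 2.2 places the attrition between consent and first treatment, so enrolled in 2.5.1 could mean having started treatment, with 99 consented. That reading is possible, but Figure 1 describes the 198 as randomized and sets 90 and 135 beside them. Starting treatment is also not the same as having a Post-aiTBS MADRS. The ambiguity stands and needs settling in the text.

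The harm is small, and this objection stands in full. A reader might infer that early looks undermine the trial's power or error control. The calculation does not support that: power moves by about half a percentage point and type I error stays at about 1.9%.

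A reader might also take the attrition slip for an undersized trial. One or two participants on an anticipated 10% is rounding-level.

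The strongest tempting reading is that the 150 is simply wrong and the savings are overstated. The document does not support that.

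- The SD, the posterior model and the other arm's effect are not given, and the SD had to be re-solved for each scenario. At a fixed SD of 7.35 with both arms at 4 points, expected N is 148, though power is then 89%.
- With power pushed to about 84% and the other arm also effective, expected N is about 154.
- The match at 147 does not validate the 4-point result, because the null figure does not depend on the SD.
- The model gives 1.9% type I error against the stated 2.5%, so it is not shown to be the sponsor's simulator.
- Section 2.3 describes these as example scenarios from the initial design phases.

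Nor is there a discrepancy at 5 points, since 137 reproduces.

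**Conclusion.** The contradiction over the interim trigger is real and rests on the article's own words. The written trigger is not the design whose null expected sample size is reported. Its practical size is modest: about 81 instead of 90 analysable participants at the first look, and a fall in early success at 4 points from about 24% to 21%, assuming SD 7.35 and a null second arm. Confidence in this part is high.

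The attrition arithmetic is certainly off, by 1 to 2 participants, and is minor.

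The 150 is a low-confidence query only. If the assumptions above hold, it is about 5 to 10 participants low, and the average saving against 198 would be 38 to 43 (198 − 160 to 198 − 155) instead of 48 (198 − 150). It drives no decision rule.

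**What to change.** In section 2.5.1 and the Figure 1 caption, state that the interim analyses are triggered when the 90th and 135th participants have a Post-aiTBS MADRS. This costs one sentence. At 10% attrition the looks then fall at about 100 and 150 enrolled, close to the 99 and 148 already used in section 2.3, so no sample size changes.

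In the same edit, either restate the analysable range in section 2.2 as 89–178 for 99–198 enrolled, or restate enrolment as 100–200 for 90–180 analysable. The first option needs no extra participants; the second adds two at the maximum.

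Check the expected sample size of 150 at 4 points against the existing simulation report, and give the SD and the other arm's effect beside it. If the report confirms 150 under those inputs, nothing else changes.

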#### Analysis of primary safety outcome

2.5.2

For adverse events (AEs) with low incidence rates, resulting in sample sizes below that required for formal statistical treatment, descriptive statistics will be utilized. For events with rates above 10%, where formal statistical tests are possible, we will utilize chi-squared tests between the sham and pooled active arms to test for an increased risk in the active arms.

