The mechanism underlying the presence of depressive symptoms following military concussion is thought to involve unique multifactorial biological and psychosocial contributors. Notably, individual resting state fMRI-based network mapping has revealed different patterns of functional connectivity in patients with TBI plus depression symptoms compared with patients with TBI without depression symptoms or patients with depression symptoms in the absence of TBI (16). Thus, symptom-targeted, neural circuit-based approaches such as repetitive transcranial magnetic stimulation (rTMS) may be more effective than medications for this population. The FDA cleared rTMS for the treatment of adult treatment-resistant MDD based on trials in patients without co-occurring neurological disorders in 2008 (17, 18). Additionally, an aiTBS protocol, “SNT,” was FDA cleared following a 2022 trial for treatment resistant MDD (19). In this trial, SNT, which involves 10 sessions per day of a specific aiTBS protocol over the course of 5 days, resulted in a 79% remission rate based on a Montgomery-Asberg Depression Rating Scale (MADRS) score of less than 10, the remission cutoff. Of particular relevance to concussion, evidence suggests that rTMS may promote reorganization of brain networks which may enhance recovery following injury (20). This finding is also in-line with data supporting the use of TMS in post-stroke recovery. However, historically, a history of concussion (or any TBI) has been exclusionary for rTMS studies; thus, there is a paucity of literature on the safety and efficacy of rTMS in this population.

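### The safety analysis compares arms only for adverse events above an undefined 10% rate, on the mistaken ground that lower rates cannot be tested, and only against the pooled active arms

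*Protocol article*

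**What the plan says.** Section 2.5.2 (Analysis of primary safety outcome) divides adverse events by frequency. For the rarer ones: "For adverse events (AEs) with low incidence rates, resulting in sample sizes below that required for formal statistical treatment, descriptive statistics will be utilized". For the others: "For events with rates above 10%, where formal statistical tests are possible, we will utilize chi-squared tests between the sham and pooled active arms". The comparison is specified as "chi-squared tests between the sham and pooled active arms to test for an increased risk in the active arms".

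The section names no method for a between-arm comparison of rarer events and no comparison of a single active arm with sham. It does not say whether the 10% refers to all participants, to the pooled active group or to any one arm.

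Section 2.2 (Participants) gives the analysed size as "accounting for 90–180 participants with primary outcome measures for analysis", and section 2.5.1 starts by "enrolling all three arms (sham and 2 active arms) in a 1:1:1 allocation". On safety evidence after concussion, the Introduction says: "thus, there is a paucity of literature on the safety and efficacy of rTMS in this population".

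**The concern.** The rule treats 10% as the point below which formal comparison is impossible. No such point exists. Fisher's exact test and exact intervals for a risk difference are valid at any count; what falls with the rate is precision, and an interval shows that directly.

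Because the reference group for the 10% is not named, the same data can be tested under one reading and not under another. That choice could be made after the event counts are known.

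The two active arms differ in how the target is chosen, and comparing the targeting methods is a stated objective. A comparison against the pooled active arms alone is not suited to a harm that belongs to one method.

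What is at stake is how clearly the trial can speak about harm in a population whose safety data it describes as scarce. A sizeable imbalance could be reported with neither an interval nor a test beside it.

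**Working it through.** **Inputs.** The analysed maximum is 180 (section 2.2); the article's enrolment range follows as 180 × 1.10 = 198 and 90 × 1.10 = 99. Allocation is 1:1:1, and 2:1 active to sham after an arm is dropped (section 2.5.1), so sham stays at one third: 60 sham and 120 active at 180, 45 and 90 at 135, 30 and 60 at 90. The article gives no power, alpha, sidedness or event rates for safety. I assume two-sided 0.05, and the event counts and rates are illustrative.

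**Step 1: excesses at or below the cut.** Overall rate = (active events + sham events) / total. P-values are Fisher two-sided.

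| Active | Sham | Overall rate | Pooled active rate | p |
|---|---|---|---|---|
| 12/120 | 0/60 | 12/180 = 6.7% | 10.0% | 0.009 |
| 17/120 | 0/60 | 17/180 = 9.4% | 14.2% | 0.0008 |
| 13/90 | 0/45 | 13/135 = 9.6% | 14.4% | 0.005 |
| 9/60 | 0/30 | 9/90 = 10.0% | 15.0% | 0.027 |
| 8/60 | 1/30 | 9/90 = 10.0% | 13.3% | 0.26 |

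If the overall rate is meant, none of these rows is above 10% and none is tested. If the pooled active rate is meant, only the first row stays untested, since 12/120 is exactly 10%. If the rate in any single arm is meant, the first row is tested unless the 12 events split 6 and 6, because 7/60 = 11.7%. The problem is largest at 180 and small at 90.

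**Step 2: how often this could happen.** Assume true risks of 10% active and 0% sham at 120 v 60. Enumerating the binomial outcomes:
- Fisher two-sided p<0.05: 86% of trials.
- Overall rate above 10% (more than 18 events in 180): 3% of trials.
- Pooled active rate above 10% (more than 12 events in 120): 42% of trials.

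With 1% rather than 0% in sham, Fisher's test is significant in 62% of trials and the overall rate exceeds 10% in 5%.

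**Step 3: a harm confined to one arm, above the cut.** Take 60 per arm with 3 (sham), 3 and 13 events. The overall rate is 19/180 = 10.6%, so the event is tested. Chi-squared without continuity correction:
- Pooled, 16/120 v 3/60: p=0.086.
- Affected arm, 13/60 v 3/60: p=0.007, unadjusted for two arm-level comparisons (Fisher 0.014).

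In terms of power, with true rates of 5%, 5% and 20%, a normal approximation gives 33% pooled and 70% for the affected arm.

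**Step 4: dependence on arm dropping.** If the harm sits in one arm, the pooled excess equals the arm's excess times that arm's share of the pooled active group.
- No arm dropped: 60/120 = one half.
- Arm dropped at 90: the remaining 90 participants split 60 active and 30 sham, giving 90 surviving arm, 30 dropped arm and 60 sham. The share is 90/120 = three quarters for the surviving arm and 30/120 = one quarter for the dropped arm.

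With that layout, 9 events in the surviving arm only give Fisher p=0.011 for 9/90 v 0/60 and p=0.030 pooled (9/120 v 0/60), so little is lost. A harm confined to the dropped arm is diluted most.

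**The case against.** Describing uncommon adverse events and testing only common ones is customary. Descriptive statistics in a randomised trial ordinarily include counts and rates by arm, so a split such as 12 v 0 would be visible. A reader might infer that the rule strips such signals from the report or leads to a conclusion of no increased risk; the text says neither. This part of the objection stands.

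A reader might also say that 12/120 v 0/60 goes untested however the 10% is read. It does not: a per-arm reading triggers the test for any split other than 6 and 6. What stands is that the article leaves the reading open.

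Pooling is defensible. Both active arms share the session schedule and the intensity rule and differ in targeting, so pooling gives the most power for a harm of stimulation in general. An arm-specific harm above 10% does enter the pooled test, so calling it untested would be wrong. Halving the excess applies only if both active arms run to the end, and the 60% dropping rule makes that far from certain.

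It is also tempting to argue that chi-squared is unreliable in a trial of 90, where a 10% rate gives an expected sham count of 0.10 × 30 = 3. At 60 v 30 with rates of 10% to 15% its type I error stays at about 4% to 5%, so that argument carries little weight.

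Finally, the SAP is not shown and may hold arm-level tables. Their absence here is no finding. The gate, the reason given for it and the pooled comparison are stated in the article, and the point rests on those.

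**Conclusion.** The point holds in a limited form. Section 2.5.2 restricts between-arm comparison to events above 10%, gives an incorrect reason and does not define the rate. At the maximum size, an excess as large as 17/120 v 0/60 (p=0.0008) gets description only if the overall rate is meant. The same holds for 12/120 v 0/60 (p=0.009) if the overall or pooled active rate is meant. For harms above the cut that belong to one targeting method, the pooled comparison dilutes the signal without leaving it untested, by an amount that depends on arm dropping.

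These sizes rest on assumed event counts and rates, an assumed two-sided 0.05, and full enrolment to 180 for the largest effects; the 3, 3 and 13 example also needs all three arms to reach 60. The document does not support saying that signals would disappear from the report. The change is worth making because it is cheap and concerns a question that the trial itself describes as open.

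**What to change.** In section 2.5.2:

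- Remove the 10% gate and the statement that lower rates do not allow formal treatment.
- At any rate, report the number of participants with at least one event and the risk difference with an exact 95% confidence interval, adding Fisher's exact p-value if a test is wanted.
- Give this for pooled active v sham and for each active arm v sham.
- Label the results as estimation without multiplicity control.

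If a frequency threshold is kept for any purpose, state whose rate it refers to.

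The cost is a change of wording and some extra table columns, with no new data and no effect on sample size. The downside is more unadjusted safety comparisons, some of which will look notable by chance; the label is there to limit over-reading.
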